#### Internal consistency reliability

3.1.1

Internal consistency reliability will be assessed for each of the five substances using McDonald's Hierarchical Omega (ω_*h*_). Hierarchical Omega estimates the reliability of a general factor in potentially multidimensional scales [36,37] which is expected to be the case in this analysis. Additional coefficients (Total Omega [ω_*T*_] and Cronbach's Alpha [α]) will also be calculated and reported for completeness. Importantly, since SSIs contain a small number of items (five for tobacco, or six for the remaining substances), bootstrapping will be used to approximate the distribution of the all coefficients within a given range, using *n* = 10,000 samples to accommodate biases related to too few scale items [38]. This will calculate a distribution of values for each coefficient, which we could reasonably expect from our sample. A significant (two-tailed *p* < 0.05) ω_*h*_ coefficient ≥0.7 will indicate acceptable internal consistency reliability.

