#### Test-retest reliability

3.1.2

Test-retest reliability will be assessed by asking participants to complete the app twice within a period of between 7 and 28 days. Reliability will be indicated through Intraclass Correlation Coefficients (ICC_3,1_ [two-way, mixed-effects, absolute agreement, single rater]) at the scale level. ICC values for each item will also be calculated and reported for completeness. Significant (two-tailed *p* < 0.05) ICC ≥0.5 will indicate acceptable agreement [39,40].

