### Sample Size and Power Calculations

**3.5**

For the validity assessments, a series of power calculations were conducted to determine the minimum sample size needed to detect a large between-groups effect, with type-I, and type-II error rates of 5 % (corresponding to α = 0.05), and 10 % (corresponding to an *a priori* power of 90 %) respectively. Where possible, we will also aim to recruit a 1:1 ratio of participants for each group (i.e., positive/negative cases), and so a 1:1 ratio of participants was used here. Using these parameters as default, we conducted the following power calculations in G-power [43].

For each regression model assessing concurrent validity, it was determined that a minimum of 111 participants are needed for each model (corresponding to line-of-best-fit slope of 0.3). For each logistic regression model assessing concurrent validity with the independent assessment, a total sample size of 62 using each substance was determined. The additional parameters used in this analysis included a probability of reaching diagnosis in the diagnosis present group of 0.70 (corresponding to a sensitivity of 70 % and an Odds Ratio of 2.33 [0.70/0.30]), versus a chance probability (i.e., 50%) in the diagnosis absent group. These parameters yielded a total sample size of 62 individuals (approximately 31 in each group diagnosis present/absent assuming 1:1 sampling). For each ANOVA model assessing discriminant validity, a minimum of 96 participants using each substance are required to power the analysis (corresponding to *η*^2^ = 0.14 [44]). Based on this, the minimum number of participants to detect a large effect (Cohens’ *d* > 0.80 [45]) was 38 participants for each group. This corresponds to thirty-eight low risk, thirty-eight moderate risk, and thirty-eight high-risk individuals for each substance (which equals approximately 114 participants for each given substance). For the reliability assessment, we also calculated the minimum sample size required to detect reliability coefficients >0.70, setting the type-I error rate to 0.05, with a minimum power of 0.90, with the number of scale items equal to 4 (tobacco) or 5 (all other substances). This method has been suggested previously [46] and has been used widely in health and medical research settings [47]. The result was a minimum sample size of 38 for a 5-item scale, and 40 for the 4-item scale. We elected to use 40 as the minimum sample size required for consistency.

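### The 90% power stated for the reliability sample sizes of 38 and 40 does not apply to the rule that hierarchical omega must reach 0.7

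*Protocol article*

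**What the plan says.** Section 3.5 (Sample Size and Power Calculations) describes the reliability calculation as giving "the minimum sample size required to detect reliability coefficients >0.70, setting the type-I error rate to 0.05, with a minimum power of 0.90", using 4 items for tobacco and 5 for the other substances. It reports: "The result was a minimum sample size of 38 for a 5-item scale, and 40 for the 4-item scale". It adopts 40 as the minimum. For this calculation it names no null value, no sidedness and no particular coefficient, and refers to a cited method.

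Section 3.1.1 makes McDonald's hierarchical omega the main coefficient for each substance; total omega and Cronbach's alpha are additional. The rule is that a significant (two-tailed 5%) "coefficient ≥0.7 will indicate acceptable internal consistency reliability". It expects the scales may be multidimensional and plans 10,000 bootstrap samples for every coefficient.

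Section 2.2.2 (Recruitment) aims for at least 40 people at each of three risk levels for each substance.

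**The concern.** A power figure belongs to a particular test: a null, an assumed true value and a rejection rule. Section 3.5 gives the power but not the null, and its wording suggests that any coefficient above 0.70 would be detected with at least 90% probability. Beside the 0.7 criterion in section 3.1.1, this reads as a 90% chance that a scale above 0.70 will be declared acceptable.

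Reliability is listed among the primary outcomes in section 3 and is judged separately for five substances. If the stated power does not belong to the rule, a scale with adequate reliability could miss 0.7 by sampling error and be read as deficient on the strength of an apparently well-powered test.

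**Working it through.** **Inputs.** From section 3.5: type-I error 0.05, power 0.90, coefficient 0.70, k = 4 or 5 items, n = 40 or 38. From section 3.1.1: pass mark 0.7. From section 2.2.2: 3 × 40 = 120 per substance. Assumptions: the null value; a two-sided test; coefficient alpha with parallel normal items.

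**1. Reproduce 38 and 40.** For true reliability ρ, (1 − ρ)/(1 − estimate) follows F with n − 1 and (n − 1)(k − 1) degrees of freedom. Let c be its 97.5% point. The power for null ρ0 and true ρ1 is P(F > c(1 − ρ1)/(1 − ρ0)).

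With ρ0 = 0.30 and ρ1 = 0.70, (1 − ρ1)/(1 − ρ0) = 0.30/0.70 = 0.4286.

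- k = 4, n = 40: c = 1.624, threshold 0.696, power 0.902. At n = 39, power is 0.895.
- k = 5, n = 38: c = 1.609, threshold 0.690, power 0.907. At n = 37, power is 0.8995.

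Both printed figures are matched exactly.

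**2. Is the null unique?** Power depends only on the ratio above, so several pairs fit.

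| Null | True value | n, 4 items | n, 5 items |
|---|---|---|---|
| 0.30 | 0.70 | 40 | 38 |
| 0.70 | 0.871 | 40 | 38 |
| 0.65 | 0.85 | 40 | 38 |
| 0 | 0.70 | 21 | 19 |
| 0.50 | 0.70 | 108 | 101 |
| 0.70 | 0.80 | 170 | 159 |

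With the true value fixed at 0.70, only a null of 0.300 to 0.302 gives both figures. That pair is the most natural inference, because 0.70 is the only coefficient section 3.5 names. A null of 0.70 also fits, but then 90% power exists only at a true value near 0.87; at 0.80 the sizes would have to be 170 and 159.

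**3. The section 3.1.1 rule.** If significance is judged against zero, at n = 40 and k = 4 an estimate is significant above 1 − 1/1.624 = 0.384. Any estimate of 0.7 clears that, so the rule reduces to the estimate reaching 0.7. The chance of passing is P(F ≥ (1 − ρ)/0.30). The ratio is 0.29/0.30 = 0.967 at ρ = 0.71 and 0.25/0.30 = 0.833 at ρ = 0.75.

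| True value | n = 40 (4 to 6 items) | n = 120 (4 to 6 items) |
|---|---|---|
| 0.71 | 53% | 58% |
| 0.75 | 74–75% | 88–89% |
| 0.78 | 87–88% | 98% |
| 0.80 | 93% | over 99% |
| True value giving 90% | about 0.79 | 0.752–0.754 |

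**4. Stricter reading.** If significant means significantly above 0.70, a 90% chance needs a true value of about 0.87 at n = 40 or 0.81 at n = 120.

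**5. Item counts.** Section 3.1.1 gives five items for tobacco and six for the others, where section 3.5 uses four and five. With five and six items the test in step 1 needs 38 and 36, so 40 still covers it; the counts should be reconciled.

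**The case against.** The strongest reply is that the calculation may be sound. The article cites a method and refers to a detailed analysis plan, where the null may be stated. If the null was 0.70 and the assumed value about 0.87, the words about coefficients above 0.70 make some sense. This stands so far as it goes: neither Cronbach's alpha nor a null of 0.30 is documented, and the article should not be said to have used them. It does not rescue the printed claim, because 90% power at 0.87 is not 90% power for coefficients above 0.70 generally.

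Second, 40 is a floor. About 120 per substance are planned, the other calculations in section 3.5 already ask for more than 40 (111 per regression, about 114 for the group comparisons), and at 120 a true 0.75 passes 88–89% of the time. This also stands. It reduces the practical consequence and means that recruitment is not at issue.

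Two stronger readings are tempting and should not be drawn.

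- A reader might set a pass chance of about 48% at a true 0.70 against the stated 90%. Any point-estimate cut-off is passed about half the time by a scale exactly at the cut-off (48% at n = 40, 49% at n = 120). No null or sample size changes that, and section 3.5 speaks of coefficients above 0.70, not at it.
- A reader might extend the point to the test-retest rule in section 3.1.2, "ICC ≥0.5 will indicate acceptable agreement". Section 3.5 does not say that its item-based calculation sizes that rule.

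**Conclusion.** The point holds in limited form. The 38 and 40 are correctly computed for some test, but the 90% power attached to them does not belong to the hierarchical omega rule. For true coefficients between 0.70 and about 0.79 at n = 40, or about 0.754 at n = 120, the chance of passing is below 90%. At a true 0.75 a scale would miss the mark about one time in four with 40 participants and about one in nine with 120.

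That the stated power fails for coefficients just above 0.70 does not depend on which null was used. The percentages rest on alpha with parallel normal items standing in for hierarchical omega. Hierarchical omega reflects only the general factor, so for multidimensional scales the true chances are, if anything, lower; their size depends on a factor structure not yet known.

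**What to change.** 1. In section 3.5, state the coefficient, null, sidedness and assumed true value actually used. If they were alpha, 0.30, two-sided and 0.70, say that 38 and 40 give 90% power to reject 0.30 when the true value is 0.70. The authors must confirm this; it should not be adopted from the reconstruction above.
2. Replace the 90% claim with the performance of the actual rule at the planned number: for example, that with about 120 per substance a 90% chance of meeting 0.7 needs a true coefficient of about 0.754 (0.79 with 40), on the stated approximation. Reconcile the item counts with section 3.1.1.
3. In section 3.1.1, report the bootstrap 95% interval beside the 0.7 benchmark, and read an estimate below 0.7 whose interval includes 0.7 as inconclusive.

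The cost is wording in the protocol and analysis plan. The bootstrap is already planned and no participants are added. The stated power becomes less favourable.

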## Discussion

4

The Pitjantjatjara ASSIST has been transformed across a number of dimensions to increase its cultural appropriateness. The next step is to assess its validity, reliability and acceptability for use with Indigenous Australian populations. Given the lack of valid, culturally appropriate and reliable instruments for detecting risky substance use, validation of *the app* adds to the growing list of community-driven initiatives aimed at closing the health gap in Australia.

A valid, reliable app detecting risky substance use in Indigenous Australian settings could reduce such use population-wide. In addition, an instrument with a high degree of diagnostic accuracy may be able to provide a greater degree of insight into the prevalence of substance use disorders (including dependence) within the Indigenous Australian population. Assuming *the app* is valid and reliable, future research will also focus on identifying the rate of substance use disorders among the Indigenous Australian community.

While there are a number of strengths of this research, there are also some potential limitations that need to be discussed. Primarily, *the app* relies on accurate self-report data, which can be a challenge in Indigenous Australian settings for a number of reasons, including stigma, shame, cultural sensitivity, and general distrust that occurs around disclosure of substance use [20,21]. *The app* used here however, is designed to address some of these challenges, by prioritising capacity for anonymous, self-assessment and feedback. Additionally, as the app is currently only in Pitjantjatjara and English, it excludes many Indigenous Australians not fluent or literate in these languages. Therefore future research will also be needed to investigate the validity and reliability of both the English version of *the app*, as well as any additional languages that are developed and added in the future.

This project acknowledges the unique challenges and strengths that Indigenous Australian communities face in addressing the harm from substance use disorders. The Pitjantjatjara ASSIST — developed largely by, and with community — serves as a reminder about the role that community should play in the development, implementation and scale-up of culturally-grounded public health strategies.

## Ethics approval and consent to participate

This study has received ethics approvals from the Aboriginal Health Research Ethics Committee (Reference ID: 04-23-1090), Southern Adelaide Clinical Human Research Ethics Committee (Reference ID: 2024/HRE00063) and The University of Adelaide Human Research Ethics Committee (Reference ID: 39,232).

## Consent for publication

Results will be published in peer-reviewed journals, presented at conferences, and shared with participants and community stakeholders via summary reports.

## Endnotes

1Yarning is a culturally sensitive communication method rooted in Indigenous storytelling traditions, increasingly utilised by non-Indigenous Australian researchers and clinicians to facilitate knowledge exchange and build relational spaces with Aboriginal and Torres Strait Islander peoples. It involves a two-way, narrative-based interaction that emphasises listening, questioning, and sharing to elicit more meaningful descriptions of one's experiences, contrasting with Western narrative concepts by prioritising relational dynamics and oral traditions over individualistic exposition.

## Data Availability

The final dataset will be de-identified and made publicly accessible.
